## Reach and effectiveness evaluation (clinical measures of UAU and HIV care, Aim 2b)

Reach and Effectiveness will be assessed using an interrupted time series with synthetic control to evaluate whether practice facilitation is associated with our primary implementation outcome (percent of patients reporting receiving an alcohol intervention since their last visit among all responding to PROS across all CNICS sites) and with our secondary effectiveness outcomes (alcohol use, ART adherence, and viral suppression) [67, 68].

An interrupted time series design allows for conducting a rigorous naturalistic study, results can be displayed graphically to intuitively represent findings, historical trend is accounted for in the analytic model, and the size of the effect can be estimated at different times post intervention dissemination [69–71]. Addition of synthetic control can improve estimation of the counterfactual condition in which the intervention was not added to the specific HIV clinics by reducing selection bias and satisfying the parallel trends assumption, which is needed for controlled interrupted time series analyses [69].

The sample will include all patients with UAU seen at each of the CNICS sites during the study. The CNICS sites that did not have the intervention will be the control sites for the interrupted time series with synthetic control. The outcomes will be expressed as a proportion per month. Therefore, the denominator for all outcomes is all patients with UAU with a visit to the participating CNICS clinics for each month of the study period. Numerators for the effectiveness outcomes are defined as follows: (1) Implementation based on patient report (primary outcome); (2) AUDIT-C score ≤ 3 women and ≤ 4 men; (3) viral suppression as indicated by HIV RNA ≤ 200 copies; and (4) high adherence to ART defined as 90% on the visual analog scale.

The analysis will be stratified or adjusted by sex, race, and social determinants of health, including housing and income. Should one of the non-intervention CNICS sites be ineligible as a control (for instance, if it is implementing a different alcohol treatment initiative) and optimal weights for synthetic control cannot be determined, we will transition to a comparative interrupted time series. The sequential roll-out of the intervention offers added resilience against temporal secular trend threats. However, we will also model each site as a main effect prior to the intervention, as well as the main effect of time prior to the intervention, and the interaction between time and the intervention. This approach allows each site to have its own pre- and post-intervention slopes relative to its comparative synthetic control, thereby accounting for potential differences between the first, second, and third sites that could arise from secular time trends. To account for potential improvement in the practice coach’s skill over the sequential roll-out, we will also conduct the interrupted time series compared to synthetic control by site to assess for effect heterogeneity. This will be an exploratory analysis as this was not a part of our initial protocol.

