### Implementation context

All implementation activities are nested within CNICS, a longitudinal, multi-site clinical cohort study of adults ≥ 18-years-old with HIV enrolled in care. An electronic health record (EHR)-based network, CNICS integrates clinical data from a large and diverse population of PWH across ten academically-affiliated HIV clinics in the US [36].CNICS prospectively collects comprehensive patient data, including validated health outcomes, across a range of diseases, as well as detailed patient reported outcomes (PROs) and behaviors at the time of clinical visits [37]. Through regular computer-based PRO administration, delivered at approximately six-month intervals, patients report on symptoms and behaviors, including alcohol use, using the Alcohol Use Disorders Identification Test-Consumption (AUDIT-C), the AUDIT, and the MINI International Neuropsychiatric interview alcohol domain (MINI) [38–40], with responses summarized and shared with providers. The PROs provide a foundation on which to embed EBIs into clinical care sites and to collect outcomes. CNICS sites have staff responsible for administration of the PRO who can link individuals to an intervention. Activities for the current study occur at three geographically diverse CNICS sites located in Boston, Massachusetts, Chapel Hill, North Carolina, and San Diego, California with a prevalence of unhealthy alcohol use ranging from 23% to 33%.

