##### Study outcomes

Our study outcomes, guided by RE-AIM, are described in Table 3 below.

**Table 3 Tab3:** Study outcomes using the RE-AIM framework

Dimension	Exemplar Use Defined by NCI	Present Study Measure
**R**each	• Percent of individuals who participate, among all patients	Percent of patients with UAU who receive an alcohol EBI
	• Characteristics of participants compared to non-participants or to target population	Above measure compared across racial/ethnic groups, gender, and clinical characteristics
**E**ffectiveness	• Measure of primary or broader outcomes	1) Reduced UAU (AUDIT-C score < 3/4 women/men)* 2) Viral suppression (HIV-RNA < 200) 3) ART adherence (> 90%) 4) PEth
**A**doption	• Use of qualitative methods to understand adoption at setting level • Use of qualitative methods to understand staff participation	Barriers and facilitators to delivering alcohol EBIs, intervention components important to enhancing delivery and site preferences related to selection of computer or person delivered intervention.
	• Percent of staff invited that participate	1) Provider report of delivering alcohol EBIs 2) Percent of providers prescribing AUD pharmacotherapy among all clinic providers
**I**mplementation	• Percent of intervention delivery or calls completed, etc. (e.g., adherence or consistency)	1) Percent of patients reporting receiving an alcohol intervention since their last visit among all responding to the PROs 2) Percent of alcohol treatment sessions completed
**M**aintenance	• Measure of primary outcome (with or without comparison to a public health goal) at ≥6mo follow-up after final intervention contact	Percent of patients reporting receiving an alcohol intervention in the past six months among all responding to PROs at six months post final contact with Practice Coach

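### The primary outcome is given two incompatible denominators: everyone answering the patient-reported outcome survey, and patients with unhealthy alcohol use who had a visit that month

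*Protocol article*

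**What the plan says.** The section on the reach and effectiveness evaluation (Aim 2b) opens by defining the primary implementation outcome as "percent of patients reporting receiving an alcohol intervention since their last visit among all responding to PROS across all CNICS sites". The Implementation row of Table 3 has the same denominator: "Percent of patients reporting receiving an alcohol intervention since their last visit among all responding to the PROs".

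The third paragraph of the Aim 2b section restricts the analysis set: "The sample will include all patients with UAU seen at each of the CNICS sites during the study". It then states that "the denominator for all outcomes is all patients with UAU with a visit to the participating CNICS clinics for each month of the study period". The list of numerators that follows begins with "1) Implementation based on patient report (primary outcome"), so the rule explicitly covers the primary outcome.

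Three further statements bear on the point:

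- The numerator is a PRO item added for this study (section on patient-reported data through the CNICS PRO).
- PROs are given about every six months (Implementation context).
- UAU prevalence at the three intervention sites is 23% to 33% (Implementation context).

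**The concern.** The two denominators describe different populations, and each brings in a different influence unrelated to how much alcohol care patients with UAU receive.

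- **All PRO responders.** Most of these patients do not have UAU, and most of those have no indication for an alcohol intervention. The exception is patients who have dropped below the threshold and receive CBI Prize. A gain among patients with UAU is diluted, and the outcome shifts when UAU prevalence shifts.
- **All patients with UAU and a visit.** A visitor who answered no PRO cannot enter the numerator. If such visitors stay in the denominator as untreated, the outcome rises or falls with PRO completion even when care is unchanged.

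This is the primary outcome of an interrupted time series with synthetic control. The control weights are fitted to the pre-intervention outcome series, so the denominator can change the counterfactual as well as the level. The detectable effect of 0.25 to 0.5 standard deviations under Power considerations is not tied to either series. Left open, the denominator could be chosen after results are seen.

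**Working it through.** The article gives no expected value for the primary outcome, so there is no stated figure to reproduce. Simple proportions show how far the two definitions can diverge.

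**Inputs**

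- p = UAU prevalence: 0.23 to 0.33 (Implementation context).
- c = share of visitors with UAU who answer the PRO: not given; assumed 0.5 to 1.
- r = share of UAU responders reporting an intervention: not given; 20% or 30% assumed for illustration.
- l = share of non-UAU responders reporting an intervention: not given; assumed 0% to 5%. It is probably above zero, because CBI Prize goes to patients now below the threshold.

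**Formulas**

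- A (all PRO responders) = p·r + (1 − p)·l, taking completion as equal in patients with and without UAU.
- B (all visitors with UAU, non-responders counted as untreated) = c·r.
- With l = 0, B/A = c/p.

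**Ratio of the two definitions, B/A**

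| c | l | p = 0.33 | p = 0.23 |
|---|---|---|---|
| 1.0 | 0 | 1/0.33 = 3.03 | 1/0.23 = 4.35 |
| 0.8 | 0 | 2.42 | 3.48 |
| 0.5 | 0 | 1.52 | 2.17 |
| 1.0 | 2% (r = 20%) | 0.20/(0.066 + 0.0134) = 2.52 | 0.20/(0.046 + 0.0154) = 3.26 |
| 1.0 | 5% (r = 20%) | 0.20/(0.066 + 0.0335) = 2.01 | 0.20/(0.046 + 0.0385) = 2.37 |
| 0.5 | 5% (r = 20%) | 0.10/0.0995 = 1.01 | 0.10/0.0845 = 1.18 |

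**Dilution under A.** With l constant, a change in r is multiplied by p. An illustrative 30-point gain among patients with UAU becomes 0.30 × 0.23 = 6.9 points to 0.30 × 0.33 = 9.9 points.

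**Prevalence shift under A** (r = 20%, l = 0). 0.23 × 0.20 = 4.6% and 0.33 × 0.20 = 6.6% for identical care of patients with UAU.

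**Completion shift under B.** With r fixed at 20%, completion rising from 60% to 80% moves the outcome from 12% to 16%. With r fixed at 30%, completion rising from 50% to 70% moves it from 15% to 21%. Under A with p = 0.28 and l = 0, the value is 0.28 × 0.20 = 5.6% throughout.

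**When is UAU status taken?** If it came from the same PRO as the outcome, c would be 1 by construction. But the same denominator serves the AUDIT-C outcome. Screening defines a positive AUDIT-C as at least 3 (women) or 4 (men). The Aim 2b numerator is at most 3 or 4, and Table 3 requires less than 3 or 4. With same-PRO classification, only patients scoring exactly at the cut-point could meet the Aim 2b numerator, and nobody could meet Table 3's. The shared denominator makes sense only if UAU is taken from an earlier PRO, and then completion matters.

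**The case against.** The strongest reply is that the sample is limited to patients with UAU, so all those responding could mean responders within that sample. That would remove the prevalence factor. Table 3 argues against it: the Reach row names its denominator ("Percent of patients with UAU who receive an alcohol EBI"), whereas the Implementation row refers to all PRO responders. Even if the reading is granted, the choice between responders and all visitors remains open.

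Several stronger inferences are tempting, and here the other side is right:

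- A reader might infer that the definitions always differ three- to fourfold. That is only the upper end, and near-equality is possible at the lowest corner of the assumed range.
- A reader might infer that PRO completion will pass for treatment delivery. The article does not say how visitors without a PRO response are scored, and such handling is commonly left to the analysis plan. Nor does Table 1 list a coach activity aimed at PRO completion. The distortion is possible, not established.
- A reader might infer that patients without UAU are never offered an intervention. The stepped care procedure gives CBI Prize to those now below unhealthy levels.
- A reader might count Table 3's Reach row as a third primary definition. It is a separate RE-AIM measure, although the Aim 2b section uses the labels Reach, implementation and effectiveness loosely.

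None of this removes the conflict between the two stated denominators.

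**Conclusion.** The contradiction stands and must be fixed. It lies in the wording of the primary outcome itself, so it is not detail that a condensed article may leave out.

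Its size is conditional. The factor is 3.03 to 4.35 if PRO response is near complete and only patients with UAU report an intervention. It is about 1.5 to 2.2 at an assumed 50% completion with no non-UAU reports, and lower still if patients without UAU report care. Only the prevalence range comes from the article; the completion and report rates are illustrative.

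The two distortions are alternatives. The largest gap needs complete PRO response, whereas the completion artefact needs incomplete response and non-responders counted as untreated. They do not occur together at full size.

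**What to change.** - State one primary denominator, in identical words, in the Aim 2b section and the Implementation row of Table 3. The preferred choice is patients with UAU at a prior PRO who answered the intervention item in that month.
- State how visitors with UAU but no PRO response are counted.
- Report PRO completion per site and month beside the primary outcome.
- Keep the all-responder proportion as a secondary descriptive measure.

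The abstract states no denominator and needs no change. The cost is wording only, since the data are already being collected. The preferred denominator has drawbacks: monthly counts are smaller than with all responders, patients without a prior PRO are excluded, and the outcome still depends on who responds, which is why completion should be shown alongside.

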##### **EHR data**

We will collect patient demographics, HIV1-RNA, CD4 cell count, and alcohol pharmacotherapy prescription from the EHR using the CNICS data collection infrastructure [36].

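### One visit-based denominator is set for all Aim 2b outcomes without requiring a viral load or PRO that month, and it contradicts the PRO-responder denominator given for the primary outcome

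*Protocol article*

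**What the plan says.** The Aim 2b section of the protocol article fixes the unit of analysis first: "The outcomes will be expressed as a proportion per month". It then sets a single denominator: "the denominator for all outcomes is all patients with UAU with a visit to the participating CNICS clinics for each month of the study period". The numerators follow. They are patient-reported receipt of alcohol care (primary), an AUDIT-C threshold, "viral suppression as indicated by HIV RNA" at or below 200 copies, and "high adherence to ART defined as 90% on the visual analog scale". No measurement window is given for any of them.

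The opening of the same section describes the primary outcome differently, as "percent of patients reporting receiving an alcohol intervention since their last visit among all responding to PROS across all CNICS sites". Table 3 also uses PRO responders as the base for its Implementation and Maintenance percentages.

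On data sources, the Implementation context section says of the PROs: "Through regular computer-based PRO administration, delivered at approximately six-month intervals". AUDIT-C, the adherence scale and the added question on receipt of an alcohol intervention all come from that instrument. Viral load comes from routine records: "We will collect patient demographics, HIV1-RNA, CD4 cell count, and alcohol pharmacotherapy prescription from the EHR". Nothing says that either is obtained at every visit.

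**The concern.** A monthly proportion is interpretable only if everyone in the denominator could have entered the numerator. Here the denominator depends on attendance, while the numerators depend on a test or questionnaire that many attendances will not include. Taken as written, a patient with UAU who attends in a month without a PRO or viral load stays in the denominator and cannot count as a success. This applies to all four outcomes.

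The series would then mix two quantities: the outcome among those measured and the share who were measured. If the second changes at the three intervention sites after the start, and not at the control sites, the analysis can report a gain or loss that did not occur, or miss one that did. Viral suppression and adherence are the only HIV outcomes in Table 3, so an artefact in either direction would matter for interpretation.

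**Working it through.** **Step 1. Set the definitions side by side.**

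| Outcome | Source of numerator | Denominator stated |
|---|---|---|
| Receipt of alcohol intervention (primary) | PRO item, about six-monthly | PRO responders (opening of Aim 2b section; Table 3) and, later in the section, all UAU patients with a visit in the month |
| AUDIT-C threshold | PRO, about six-monthly | All UAU patients with a visit in the month |
| ART adherence | PRO visual analog scale, about six-monthly | As above |
| Viral suppression | HIV RNA in the EHR, frequency not stated | As above |

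The first row contradicts itself. In the other three, the denominator is wider than the group in which the outcome can be observed, unless an earlier value is carried forward.

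**Step 2. Write down the literal rule.** The article gives no share measured, visit rate or baseline suppression, so it has no figure to reproduce. Every input below is an assumption. Let s be the true proportion among those measured, m the share of baseline patient-months with a same-month result, and e the added patient-months without a result as a fraction of baseline. Then

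observed = s × m / (1 + e).

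**Step 3. Stable measurement (e = 0, m constant).** With s from 0.80 to 0.90 and m from 0.6 to 1.0, the series reads between 0.80 × 0.6 = 0.48 and 0.90 × 1.0 = 0.90. No false change arises. A true change shrinks, however: at m = 0.6, a rise in s from 0.80 to 0.90 reads 0.48 to 0.54, which is 6 points and not 10.

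**Step 4. More unmeasured patient-months at intervention sites.** With s = 0.85, m = 0.70 and e = 0.10, 0.85 × 0.70 = 0.595 becomes 0.595 / 1.10 = 0.541, a spurious drop of 5.4 points. Over s = 0.80 to 0.90 and m = 0.6 to 1.0, the drops are:

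| e | Spurious drop (percentage points) |
|---|---|
| 0 | 0 |
| 5% | 2 to 4 |
| 10% | 4 to 8 |
| 20% | 8 to 15 |
| 30% | 11 to 21 |

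**Step 5. PRO-based adherence.** With one PRO per six months and v visit-months per six months, the share measured is 1/v, and observed = a / v for true adherence a.

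| a | v = 1 | v = 1.5 | v = 2 | v = 3 |
|---|---|---|---|---|
| 0.90 | 0.90 | 0.60 | 0.45 | 0.30 |
| 0.70 | 0.70 | 0.47 | 0.35 | 0.23 |

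The bias can also be favourable. If the share of visit-months with a PRO rises from 1/2 to 2/3, a constant a = 0.90 reads 0.45 and then 0.60, a false gain of 15 points. If true adherence falls from 0.90 to 0.70 at the same time, the series moves from 0.45 to 0.70 × 2/3 = 0.467, so a real fall of 20 points shows as a small rise.

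**Step 6. Could measurement change at intervention sites only?** The Clinical intervention section counts alcohol screening as part of stepped care, and the Screening section says it is done by tablet PRO. The Background lists inconsistent screening among the barriers and presents practice facilitation as a way to address barriers. A change in PRO completion at the three sites is therefore plausible. A synthetic control weighted on the pre-intervention period cannot remove a measurement change that begins with the intervention and occurs only at the treated sites.

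**Step 7. With a measured-only denominator or a most-recent-value rule.** The observed proportion equals s or a whatever m, e and v are, provided that measurement is unrelated to outcome.

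**The case against.** The strongest reply is that scoring an unmeasured month as a failure is an inference. The article states no window and no rule for missing values, and a most-recent-value numerator fits its text. Some carrying forward is arguably implied: UAU status itself comes from a PRO, and an AUDIT-C outcome among patients with UAU makes sense only if that status was set earlier. A look-back may well sit in a full protocol or analysis plan that is not shown, and its absence from an article is no fault. This stands. It does not remove the contradiction over the primary outcome, or the fact that one rule is expressly applied to all outcomes.

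A reader might also infer that extra alcohol-care visits will make HIV control appear to worsen. The article does not support this as a stated feature. The second intervention takes place at the next scheduled visit, where the PRO is repeated. CBT4CBT is online, and face-to-face or telemedicine contact is listed as a mode of delivery, not as added visits. The denominator counts patients with a visit in the month, so a second contact in the same month adds nothing. Added unmeasured patient-months remain only a possibility.

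Three further points are fair. A stable unmeasured share is largely absorbed by a design that estimates change against a matched control. PRO screening is described as part of routine care, so a change in completion is plausible and not established. A measured-only denominator brings selection of its own if testing depends on how the patient is doing.

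**Conclusion.** The point holds as a defect in a stated rule. The single denominator is not conditional on measurement, and it conflicts with the PRO-responder denominator for the primary outcome in the same section and in Table 3. Followed literally, it makes all four series depend partly on measurement frequency.

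The size of any bias cannot be derived from the document. The figures above show only that it could range from nil, when measurement is stable and no unmeasured months are added, to a size that matters, in either direction. They rest on assumed values of s, m, e, a and v and on the same-month reading. The document does not show that HIV outcomes will falsely appear to deteriorate.

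This should be fixed, but it need not hold up the study. Viral suppression, adherence and alcohol use are secondary in a Hybrid Type 3 study, and for the primary outcome the remedy is to settle which of two stated denominators applies.

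**What to change.** In the Aim 2b section, replace the single denominator with one for each outcome. Use PRO responders for the primary outcome, AUDIT-C and adherence, and patients with a viral load for suppression. Alternatively, score the most recent value within a fixed look-back, applied identically at all sites and in all periods. Make the primary outcome's denominator agree with Table 3, and say whether responders means all responders or those with UAU, since the sample is described as patients with UAU.

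Beside each series, report the proportion measured by month for intervention and control sites. This shows whether measurement changed after the start and lets a reader judge the assumption behind a measured-only denominator.

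The cost is a change of wording and one added descriptive series, from data that CNICS already collects. The downsides are smaller monthly denominators, or some smoothing if a look-back is used, and the assumption under a measured-only denominator that being measured is unrelated to the outcome.

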## Abstract

**Background:**

Despite availability of evidence-based alcohol reduction interventions (EBIs), unhealthy alcohol use (UAU) remains a barrier to HIV medication adherence, viral suppression, and retention in HIV care. While translation of alcohol EBIs into HIV clinical practice is important for comprehensive HIV care, their implementation in HIV settings is impeded by resource constraints, workflow challenges, and negative perceptions of alcohol-related care.

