Implementation of EBIs for UAU in clinical settings is challenged by provider- and clinic-level barriers including lack of time and resources, inconsistent screening, inadequate training in managing UAU, operational workflows, and low confidence in the use of alcohol pharmacotherapy [24]. Practice facilitation is a multilevel intervention implementation strategy that addresses barriers to implementation of evidence-based practices. With practice facilitation, a practice coach offers tools, resources, hands-on guidance, and content expertise to assist the team in developing strategies to successfully implement an evidence-based practice [25–27]. Support by a practice coach is provided in near-real time and optimized by relationship development with each clinic site. There is substantial evidence in favor of practice facilitation in primary care, and multiple studies are using practice facilitation to implement alcohol EBIs [23, 25, 27–30]. Based on evidence in primary care settings [31, 32], practice facilitation for implementing alcohol EBIs may hold great promise for improving access to care in HIV clinics.

We are conducting a novel study in HIV clinics in which we will test practice facilitation to implement stepped care for UAU. In this manuscript, we describe the protocol of our Hybrid Type 3 effectiveness-implementation study guided by the RE-AIM (Reach, Effectiveness, Adoption, Implementation and Maintenance) evaluation framework [33]. Our study tests whether external practice facilitation increases reach, adoption, implementation, and maintenance of stepped care for UAU (our clinical intervention) in three Center for AIDS Research (CFAR) Network of Integrated Clinical Systems (CNICS) HIV clinics. We will secondarily test whether practice facilitation is associated with decreased UAU and improved ART adherence and viral suppression at the patient level (**e**ffectiveness). Formative and summative evaluations – guided by the Consolidated Framework for Implementation Research (CFIR) [34] - will also be used to tailor the implementation supports provided throughout the trial and characterize barriers and facilitators to implementation.

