This study will not be without limitations. CNICS clinics have built in data capture systems along with routine assessment of patient reported outcomes that facilitate screening and intervention, along with dedicated staff who can assist with positive screens. As such, these clinics are not likely representative of all HIV clinics, and the focus of practice facilitation activities may differ in non-CNICS settings. Further, while the quasi-experimental approach applies cutting edge implementation science methods to evaluate the intervention, it does not enable an unequivocal assessment of causality. However, a cluster randomized trial of the required size (32–40 clinics) would be extremely costly and likely infeasible, and the interrupted time series design with synthetic controls allows us to test whether the intervention is associated with improvements in both implementation and effectiveness outcomes. Additionally, in the event that a CNICS site cannot serve as a control (e.g., implementing a different alcohol treatment initiative) and optimal weights cannot be determined for synthetic control, we will move to a comparative interrupted time series. Finally, the sequential roll-out of the intervention strengthens the design by providing additional protection against threats to validity resulting from secular trends over time.

UAU among PWH disrupts optimal engagement in the HIV Care Continuum and, through it, affects viral suppression and transmission risk behaviors. With the availability of effective behavioral and pharmacological interventions for UAU, integration of alcohol EBIs into HIV clinical settings are a recommended component of comprehensive care [74]. As such, rigorously evaluating implementation strategies that may improve evidence-based alcohol screening and interventions in HIV clinical settings is essential to achieve US goals for the care of PWH and for ending the HIV epidemic.

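### Viral suppression and ART adherence are computed only among UAU patients who attend that month, so a change in who attends can bias both results

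*Protocol article*

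**What the plan says.** In the protocol article, the Reach and effectiveness section (Aim 2b) defines the sample by attendance: "The sample will include all patients with UAU seen at each of the CNICS sites during the study". It then sets the scale, "The outcomes will be expressed as a proportion per month", and one rule for every outcome: "the denominator for all outcomes is all patients with UAU with a visit to the participating CNICS clinics for each month". Viral suppression and high ART adherence are numerators over that denominator. Table 3 gives no other denominator for them and lists no retention or visit-rate outcome.

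The Background states the secondary question as whether facilitation is associated with "decreased UAU and improved ART adherence and viral suppression at the patient level".

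Two statements link drinking to attendance. The Abstract says that UAU "remains a barrier to HIV medication adherence, viral suppression, and retention in HIV care". The Discussion says: "UAU among PWH disrupts optimal engagement in the HIV Care Continuum and, through it, affects viral suppression and transmission risk behaviors".

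Planned adjustment covers sex, race and social determinants of health. Nothing is said about attendance or loss from care.

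**The concern.** By the article's own reasoning, attendance lies between drinking and suppression. If facilitation reduces unhealthy drinking, it may also change which patients turn up. Restricting the outcome to that month's attenders then conditions on something the strategy can alter.

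Patients kept in care who would otherwise have dropped out enter the denominator. If they are less well suppressed or less adherent than existing attenders, they lower the proportion even though their being in care is a benefit. Conversely, a loss of poorly controlled patients would raise the proportion with no benefit behind it.

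The planned safeguards do not reach this. The synthetic control is matched on the pre-intervention series, so it cannot remove a change in case mix that starts after roll-out and only at facilitated sites. Staggered starts protect against secular trends, which is a different threat. With no attendance series planned, a reader could not tell a real change in suppression from a change in who was counted.

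**Working it through.** The article gives no retention, visit or suppression rates, so there is no figure of its own to reproduce. Every rate below is an assumption.

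**Formulas.** Let r0 and r1 be retention among UAU patients before and after, s suppression in continuing attenders, s_new in the newly retained and s_out in those not retained. Retained patients are taken to attend equally often.

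- Visit-based proportion: before, s; after, [r0·s + (r1 − r0)·s_new] / r1. Change = (r1 − r0)/r1 × (s_new − s).
- All UAU patients: before, r0·s + (1 − r0)·s_out; after, r0·s + (r1 − r0)·s_new + (1 − r1)·s_out. Change = (r1 − r0) × (s_new − s_out).

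**Base case.** r0 = 0.80, r1 = 0.85, s = 0.88, s_new = 0.60, s_out = 0.20 or 0.40.

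- Visit-based: (0.80 × 0.88 + 0.05 × 0.60)/0.85 = 0.734/0.85 = 86.35%, against 88% before: −1.65 points.
- All UAU patients: 0.05 × (0.60 − 0.40) = +1.0 point, or 0.05 × (0.60 − 0.20) = +2.0 points.

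**Gain in continuing attenders that cancels the fall.** A gain g adds 0.80·g/0.85 to the visit-based series. Setting this to 1.65 gives g = 1.65 × 0.85/0.80 = 1.75 points. With g = 2 and s_out = 0.30, the observed change is 1.88 − 1.65 = +0.2 points, while the change in all UAU patients is 0.80 × 2 + 0.05 × 30 = +3.1 points. That is heavy attenuation without reversal.

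**No bias.** If s_new = s, the visit-based change is zero whatever r1 is, so case mix does not distort it.

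**A second model, through visit frequency.** Let 80% of UAU patients be stably in care (monthly visit probability 0.20, suppression 0.90). The other 20% are loosely retained, and their monthly visit probability rises from 0.05 to 0.10. Before, with their suppression at 0.50, the visit-based proportion is (0.16 × 0.90 + 0.01 × 0.50)/0.17 = 87.6%.

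| Suppression in the loosely retained | Visit-based after | Visit-based change | Fixed-cohort change |
|---|---|---|---|
| 0.50, unchanged | 0.154/0.18 = 85.6% | −2.1 | 0 |
| 0.50 to 0.60 | 0.156/0.18 = 86.7% | −1.0 | +2.0 |
| 0.50 to 0.80 | 0.160/0.18 = 88.9% | +1.2 | +6.0 |

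The stable share was varied from 70% to 90%, with visit probability rising from 0.05 to 0.10, 0.05 to 0.15 or 0.10 to 0.15:

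- 0.50 unchanged: the series falls 1.0 to 5.9 points with no change in the cohort.
- 0.50 to 0.60: it falls 0.2 to 3.4 points against a true rise of 1.0 to 3.0.
- 0.50 to 0.80: it rises 0.3 to 4.6 points against a true 3.0 to 9.0.
- 0.90, equal to stable patients: no bias.
- 0.95, better than stable patients: it rises 0.1 to 0.7 points with no true change.

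**The case against.** **Suppression among patients seen is a legitimate clinic-level measure.** CNICS is a cohort of people enrolled in care, the outcomes are secondary, and the article speaks of association and disclaims unequivocal causality. This stands, and it is a reason to keep the visit-based series. It does not make that series sufficient for a question posed at patient level.

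**The effect on attendance may be small.** Stepped care starts from a screen at a clinic visit, and no outreach to absent patients is described, so any retention effect must come through attenders who take up an intervention. With an assumed 30% extra reach and a 5-point retention effect, retention rises 0.30 × 5 = 1.5 points. The visit-based shift is then 1.5/81.5 × (60 − 88) = −0.5 points. This also stands: the size is open.

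**The denominator may require current UAU.** If so, patients retained because they stopped drinking at unhealthy levels leave it and do not dilute it. The article does not settle this.

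**A reader might infer that the sign always reverses.** Under the base-case formulas, with s_out at 0.20 to 0.40, s_new at 0.50 to 0.70, s at 0.88 to 0.92 and retention gains of 3 to 10 points, the observed change runs from −0.65 to −4.94 and the true change from +0.3 to +5.0, reversed throughout. That follows from the inputs: s_out lies below s_new, s_new lies below s, and continuing attenders are given no benefit. The article supplies no such rates, and its hypothesis is that adherence and suppression improve.

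**Replacing the denominator has faults of its own.** Counting missing HIV RNA as not suppressed sets s_out to 0. Once the windows have expired, the base case then shows 0.05 × 0.60 = +3.0 points against a true +1.0 to +2.0. Before expiry, a patient who leaves just after a suppressed result still counts as suppressed. So the cohort series should be an addition, not a replacement.

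**Conclusion.** The concern holds as a risk of bias in two secondary outcomes. The denominator is stated outright, and the article's own rationale makes attendance something facilitation may change. Neither the planned adjustment nor the synthetic control removes a shift that occurs after roll-out at facilitated sites only.

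The direction is against the intervention if newly retained patients are less well suppressed or adherent than existing attenders. The article's account of UAU makes that plausible but does not establish it. In the base case the distortion is enough to show a fall of about 1.65 points where the whole UAU group gains 1.0 to 2.0. That result needs a 5-point retention gain, a 28-point gap in suppression and no benefit in continuing attenders, none of which is documented. The defensible conclusion is that the visit-based series alone cannot separate an effect on suppression or adherence from a change in who attends. It does not follow that the results will have the wrong sign.

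**What to change.** Keep the visit-based proportions. Prespecify two further series, run through the same model for intervention and control sites:

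1. **Viral suppression in an in-care UAU cohort.** Membership should not depend on a visit that month: UAU fixed at an earlier qualifying PRO, a visit within a stated look-back, and the most recent HIV RNA in a stated window. Report it with missing HIV RNA counted as not suppressed and again with it excluded. If everyone not retained lacks a recent HIV RNA, the base case gives +3.0 and −1.65 points under the two rules, which bracket the true +1.0 to +2.0.
2. **Attendance.** The monthly percentage of that cohort with a recent visit. Adherence is self-reported in the PRO and not observed in non-attenders, so this series does not correct it. It does let the adherence and suppression results be read against any shift in attendance.

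Standard errors for the cohort series must allow for the autocorrelation that overlapping windows create. The near-zero autocorrelation and the detectable effect in Power considerations should not be carried over to it.

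The cost is modest programming on visit, PRO and HIV RNA data that CNICS already holds. The drawbacks are a smoother series that responds later, and transfers of care that cannot be told apart from loss.
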